### Intervention description {11a}

#### Intervention arm

Infants allocated to the SSC arm will be placed in upright, ventral SSC with their mother at least 15 min prior to data collection.

### Criteria for discontinuing or modifying allocated interventions {11b}

It is unlikely that there will be a need to modify the allocation intervention. However, parents may choose to withdraw their infant from the study for any reason at any time.

### Strategies to improve adherence to interventions {11c}

Every effort will be made to ensure the fidelity of the intervention. Any deviation will be documented using an intervention fidelity checklist completed by the research nurse at the end of the procedure. Any need for additional (e.g. rescue) pain management strategies will be monitored and compared monthly across groups.

### Relevant concomitant care permitted or prohibited during the trial {11d}

No other changes in clinical care will occur outside the study interventions.

### Provisions for post-trial care {30}

N/A: There is no post-trial care in this trial.

### Outcomes {12}

#### Noxious-related brain activity

Noxious-related brain activity will be measured from a pain-related event-related potential [14–16, 41] induced by a clinically required heel lance measured using a dense-array neonatal EEG recording. The primary outcome attributed to the clinically required heel lance will be a noxious-related N420-P560 event-related potential (ERP) which will specifically be examined and isolated at electrode Cz as previous research has reported pain-related activity at this site in both neonates [14, 16, 42] and adults [43].

The EEG data will be recorded using a 32 channel HydroCel Geodesic Sensor Net connected to a GES 400 EEG system (EGI, Eugene, OR, USA). Electrodes will be submerged for 5 min in a solution of warm water and infant shampoo. Electrode impendences will be checked to ensure they are below the impedance threshold of 100 kΩ. NetStation Acquisition software (version 5.2.0.2) will be used for recording of EEG activity from 0.5 to 30 Hz with a sampling rate of 1000 samples per second and a conversion of 24 bit. For all infants, regardless of randomization, data collection will begin with a continuous recording of a one-minute baseline of all outcome measures while the infant is resting in their incubator or cot (BL1). Following this, a non-noxious (NN1) control stimulus will be applied to the infant’s foot to capture a baseline response on EEG to a non-painful event. This non-noxious (sham) stimulus will consist of placing the heel lance against the foot and rotating it 90 degrees, so that when the lance is released it mimics the sensation of the heel lance procedure without the associated tissue-breaking and pain. The infant will then be placed in their assigned intervention group and will be re-exposed to the non-noxious control stimulus, followed by the clinical heel lance.

The method for time locking the non-noxious stimulus and noxious heel lance to the EEG recording in this study involves the use of audio-recording equipment to time-lock based on the audible spring-blade release of the heel lance. During both events, the lancet will be released. The sound of the heel lance release will be captured using a lapel microphone held by the research coordinator close to the infant’s foot, amplified through an USB audio interface (M-Audio Fast Track, M-Audio Inc., Cumberland, RI, USA), and linked to the EEG amplifier using an EGI Audio-Visual (AV) device through an AV device DIN adaptor and hypergrip cable (EGI, Eugene, OR, USA). This apparatus ensures that the sound associated with heel lance release is marked with millisecond precision on the continuous EEG recording. To test the accuracy of this time-locking method and ensure there is no latency through the audio-computer interface, the microphone input line and audio output line were connected to a digital oscilloscope and relative timing of the activity on both lines were observed during microphone activation. There was no appreciable latency between input and output, indicating a precise time-locking mechanism to isolate a pain-specific ERP.

#### Pain intensity

Pain intensity will be assessed using the Premature Infant Pain Profile—Revised (PIPP-R) [44, 45]. The original PIPP was developed by Stevens et al. in 1996 [46] and revised in 2012 [44]. The PIPP includes two physiological (heart rate, oxygen saturation), three behavioural (brow bulge, eye squeeze, nasolabial furrow), and two contextual (GA, behavioural state [BS]) variables known to modify pain responses. Each variable is scored on a four-point scale (0, 1, 2, 3) reflecting changes in magnitude from baseline values. GA and BS are reverse-scored to account for developmental and state differences in preterm and term infants abilities to respond to pain [46]. In the PIPP-R, the original seven variables of the PIPP are retained, but ordering and scoring of GA and BS has changed to ensure baseline characteristics prior to the painful event do not artificially inflate scores. The PIPP-R has demonstrated construct validation in infants of varying GAs during extreme group comparisons [44]. As facial actions are the most specific bio-behavioural indicator of acute procedural pain in newborn infants [47], the three individual facial actions within the PIPP-R will be analysed separately in addition to the composite PIPP-R score. Physiologic and behavioural data collection techniques, which have been developed and used extensively by this research team over the past decade, will be employed [48, 49]. For physiologic variables, heart rate and oxygen saturation will be measured continuously throughout the procedure via a pulse oximeter placed on the infant’s hand and recorded on the GES 400 EEG System 400 Physio 16 II. Behavioural state will be observed for 30 s prior to the noxious stimulus from video, and GA will be determined from the medical record. Time locking of the noxious-evoked stimulus and heel lance will be synchronized with EEG recordings, physiological data, and behavioural data using the time trigger device described previously. Electronic event markers will be used to synchronize all physiological and behavioural data, and to indicate four distinct phases of the standardized heel lance: (i) baseline data collection for 2 min; (ii) 2 min during and following sucrose administration; (iii) heel lance; and (iv) return to baseline for 2 min. Pain intensity will be calculated by trained coders, blinded to the study purpose and design, using newly developed facial coding software (Pain Assessment in Neonates, [PAiN]) developed recently by the Principal Investigator (PI) for previous research [38]. Inter-rater reliability of greater than 0.8 [50] with the trained coders for the PIPP-R scores will be established prior to data collection and monitored throughout the study using a random selection of infants after 20 infants are entered into the study. See Fig. 1 for overview of data collection procedures.

**Fig. 1 Fig1:**
[figure not shown]
**a** Twenty-four per cent sucrose intervention timeline. **b** SCC intervention timeline

#### Adverse events and safety monitoring

As the HydroCel Geodesic Sensor Net requires that electrode sponges are soaked in a warm saline solution prior to application to the infant scalp, a thermal cap will be placed over the sensor net during data collection to reduce heat loss. Infant axillary temperature will be monitored every 15 min throughout data collection to ensure normothermia (36.5 to 37.5 °C). Infants will be monitored constantly during data collection (observation and continuous cardiorespiratory and oxygen saturation recording) in order to prevent any risk of skin irritation while wearing the HydroCel Geodesic Sensor Net as well any incidence of choking, apnea (defined as unexplained cessation of breathing for 20 s or longer, or a shorter respiratory pause associated with bradycardia, cyanosis, pallor, and/or hypotonia [51]), or bradycardia (defined as a 30 beat per minute drop from baseline, or when the heart rate is below 100 beats per minute). Adverse events, need for a repeat heel lance to allow for sufficient blood collection, or administration of additional doses of “rescue” sucrose will also be recorded on the tolerance/adverse events section of the intervention fidelity checklist, which has been developed and validated in previous research by the PI [38].

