**Methods:**

We will randomly assign 126 babies (32 to 36 completed weeks gestational age) admitted to the neonatal intensive care unit, and their mothers within the first seven days of age to receive (i) SSC plus sterile water and (ii) 24% oral sucrose. Each baby will receive a medically indicated heel lance, following a no treatment baseline period. The primary outcome is noxious-related brain activity measured using an electroencephalogram (EEG) pain-specific event-related potential. Secondary outcomes include pain intensity measured using a bio-behavioural infant pain assessment tool (Premature Infant Pain Profile-Revised) and rate of adverse events.

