#### Secondary

Infants randomized to the SSC condition, when compared to infants randomized to the 24% oral sucrose, will demonstrate (a) less differentiation between bio-behavioural pain response and noxious-evoked pain activity elicited by clinical (heel lance) noxious stimulus and (b) fewer adverse events (i.e. episodes of choking, apnea, bradycardia, temperature instability, need for repeat heel lance or “rescue sucrose” doses).

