## Assignment of interventions: Blinding

### Who will be blinded {17a}

In keeping with clinical trials where interventions cannot be blinded, we will ensure that data will be collected independently from those conducting analysis (blinded to group allocation) to minimize bias. Mothers, staff, and research nurses and assistants completing data collection will not be blinded to whether the infant has been randomly assigned to SSC condition or the 24% oral sucrose condition. All individuals carrying out data analysis will be blinded to group assignment. Additionally, EEG data analysts will have no prior knowledge of study groups and assignment. Close up video of the infants face during the painful procedure with no sound will be recorded to ensure that coders will be blinded to all aspects of group allocation and study purpose.

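### Bradycardia, part of a directional secondary outcome, is captured on a form completed by an unblinded nurse; no text says the stored heart-rate trace or a blinded assessor supplies the compared data

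*Protocol article*

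**What the plan says.** All references are to the protocol article.

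- **Outcome and direction.** The abstract (Methods) states: "Secondary outcomes include pain intensity measured using a bio-behavioural infant pain assessment tool (Premature Infant Pain Profile-Revised) and rate of adverse events". The secondary hypothesis is that infants in SSC will show "fewer adverse events (i.e. episodes of choking, apnea, bradycardia, temperature instability", and it goes on to list repeat lance and rescue sucrose.
- **Comparison.** Under Statistical methods, binary adverse events go into a logistic model (Pain intensity section) and mean frequencies into t-tests (Adverse events section).
- **Capture.** Adverse events and safety monitoring says that events, repeat lances and rescue doses "will also be recorded on the tolerance/adverse events section of the intervention fidelity checklist". Section {11c} says: "Any deviation will be documented using an intervention fidelity checklist completed by the research nurse at the end of the procedure".
- **Blinding.** Section {17a} says that "research nurses and assistants completing data collection will not be blinded". Data analysts, EEG analysts and video coders are blinded.
- **Stored signal.** In the Pain intensity outcome section, "heart rate and oxygen saturation will be measured continuously throughout the procedure via a pulse oximeter", and the signals are recorded on the EEG system and synchronised by electronic event markers.
- **Definition.** Bradycardia is a drop of 30 beats per minute from baseline or a rate below 100. The same section refers to continuous cardiorespiratory and saturation recording while infants are monitored.

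**The concern.** Blinding the people who analyse the data cannot undo a bias that entered when an event was written down, or not written down, by someone who knew the arm. The heart-rate signal that contributes to the PIPP-R, a score calculated by blinded coders, could also be scored for bradycardia. As written, one secondary outcome is protected and the other is not.

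At stake is how a result such as fewer bradycardias with SSC could be read. If events were entered less completely in one arm, the recorded difference would mix a true effect with a recording effect, and the data as described could not separate them. The reverse pattern could hide a real benefit.

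**Working it through.** **Step 1: trace the data path for bradycardia.**

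| Question | Answer in the article | Where |
|---|---|---|
| Compared between arms? | Yes, with a stated direction | Hypotheses; Statistical methods |
| Named capture form | Tolerance/adverse events part of the fidelity checklist | Adverse events and safety monitoring |
| Who completes the form | Research nurse | {11c} |
| Blinded? | No | {17a} |
| Objective record available? | Yes, heart rate, continuous and time-marked | Pain intensity (outcome) |
| Numeric definition? | Yes | Adverse events and safety monitoring |
| Stored trace or blinded assessor named as source for the comparison? | No | – |

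**Step 2: which components the stored trace could supply.** Bradycardia: yes. Apnea: only if respiration is among the stored signals, since the outcome section names only heart rate and saturation, and part of the definition rests on observed signs. Choking, temperature instability, repeat lance and rescue sucrose: no.

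**Step 3: the plan's own figure.** No stated figure concerns adverse events. The 63 per group is used below, so it was checked against the PIPP-R inputs (difference 1, SD 2, two-sided 5%, 80% power): n = 2 × (1.96 + 0.842)² × 2² / 1² ≈ 62.8, so 63 per group. It reproduces.

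**Step 4: illustration of size.** Assumptions, none of them from the documents: the same true event rate p in both arms; proportion recorded s₁ = 90% under sucrose and s₂ under SSC. Recorded rates are then p·s₁ and p·s₂; for example, p = 20% and s₂ = 70% give 18% and 14%. With x and y recorded events among 63 infants per arm, the rejection probability is the sum of Bin(x; 63, p·s₁) × Bin(y; 63, p·s₂) over all pairs with |z| > 1.96, where z = [(x − y)/63] / √[2·p̄(1 − p̄)/63] and p̄ = (x + y)/126. This pooled test of proportions stands in for the planned models.

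| Recorded, sucrose / SSC | p = 10% | 20% | 30% | 40% |
|---|---|---|---|---|
| 90% / 90% | 5.1% | 4.7% | 5.1% | 5.2% |
| 90% / 80% | 5.6% | 5.7% | 6.7% | 7.7% |
| 90% / 70% | 7.0% | 8.9% | 12.2% | 16.1% |

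Most of these rejections favour SSC (for example, 8.4 of the 8.9 percentage points at p = 20% and 70%). Swapping the two recording proportions gives the same totals in favour of sucrose.

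**The case against.** Several counter-arguments carry weight.

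- **The continuous recording is part of safety monitoring.** A reader might infer that the plan uses the physiological record for pain and ignores it for safety. The text does not support that: the adverse event section relies on continuous recording during monitoring, and the word *also* may mean that the checklist is an additional log. What remains is that the article never says which source feeds the comparison.
- **An article condenses a fuller protocol.** Source-data detail may sit in the full version, and {22} defers collection and assessment to good clinical practice and ethics approvals. But this article does name a form, a recorder and the recorder's blinding status. The point addresses that stated arrangement.
- **The scope for bias is limited.** The checklist is described as validated, the definitions are objective, infants are watched constantly and the lance procedure lasts three to five minutes. The end-of-procedure timing in {11c} is written about deviations; it reaches adverse events only because they share the checklist. All this lessens the risk without removing it.
- **The mechanism is partly conjecture.** It is tempting to add that the nurse knows the hypothesis, or that infants in SSC are harder to observe. No section says either. Differential recording is possible, not shown.
- **A trace is not perfect.** {19} warns of physiologic data lost to equipment failure or movement. Artefact could also create false bradycardias or gaps, perhaps unequally by arm.

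**Conclusion.** The point holds for bradycardia. It is a named component of a directional secondary outcome, its only named capture form is completed by an unblinded nurse, and an objective stored signal with a matching numeric definition exists without being named as the source for the comparison. Differential recording by arm is possible and, for this component, avoidable.

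A reader might extend this to the whole adverse event comparison. The documents do not support that, because most other components cannot be read from heart rate or saturation and would stay unblinded under any feasible change.

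The size rests wholly on assumed event rates and recording proportions. A ten-point recording gap raises the false-positive rate only to 5.6% to 7.7%; a twenty-point gap raises it to 7.0% to 16.1%. The direction is unknown. The primary outcome is not affected. This is a modest weakness in a secondary outcome, worth correcting because the correction is cheap.

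**What to change.** For the between-arm comparison, derive bradycardia from the stored, time-marked heart-rate trace. Apply the protocol's own definition in a fixed script, run by analysts already blinded to arm, with an artefact rule set in advance. Use the same scoring window in both arms, and remove any marker that shows the arm, such as the sucrose phase marker. Flag unassessable segments, count them by arm, and report agreement between trace and checklist.

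Keep the checklist for immediate care and for choking, temperature, repeat lance and rescue sucrose (and apnea unless respiration is stored), and label these components as unblinded. Do not add desaturation: it is not a listed adverse event and would be a new endpoint.

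Amend the adverse event section and {17a} by a sentence each. If the full protocol already names the trace as the source, that statement alone is enough.

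The cost is a scripted extraction and a little more analysis, with no new procedure for infants or staff. Some trace will be lost to artefact. Recordings already made can be scored retrospectively if retained; {27} keeps study records for at least 10 years.

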#### Demographic and background clinical data

Demographic and background clinical data characterizing the sample that will be collected from maternal and infant hospital charts will include: maternal age, maternal parity, maternal experience providing skin-to-skin contact to previous children, maternal medications, history of maternal diabetes during pregnancy, infant GA at birth, infant postnatal age at time of study participation, mode of delivery, infant birth weight, infant Apgar scores, infant sex, total number of previous painful procedures, primary diagnoses, severity of illness (Neonatal Therapeutic Interventions Scoring System [NTISS] [52], Score for Neonatal Acute Physiology-II [SNAP II] [53], and whether the infant has a history of receiving opioids.

### Participant timeline {13}

Participant timeline is shown in Fig. 1.

### Sample size {14}

Using a priori data [15], we will require 63 participants per group (total sample size of 126 for the two groups) to detect a 30% reduction in amplitude of the pain-specific ERP on EEG during the clinically required heel lance. The sample size calculation accounts for multiple testing across intervention groups and is based on a type I error probability of 5% and power of 80% [54]. Sixty-three participants per group also allows us to detect the smallest clinically important difference of one on the PIPP-R scale, with a standard deviation of two, considered a clinically relevant difference between the active interventions of SSC and 24% oral sucrose [55].

### Recruitment {15}

Recruitment is ongoing. Based on expected number of infants admitted to the NICU within the eligible gestational age range and recruitment rates from our previous neonatal pian studies we anticipate an expected enrollment of, on average, four participants monthly. Through daily communication with the clinical team, the research team will identity potentially eligible infants and parents. Parents of eligible infants will be approached by the research nurse; information will be provided, and consent obtained.

## Assignment of interventions: allocation

### Sequence generation {16a}

Participants will be randomized to groups using a password-protected REDCap database randomization tool. Sequence generation will be conducted using a computer-generated random number list know only to a consultant statistician not associated with the study and made available through the online portal. Randomization will be block-stratified by age (32 to < 34 weeks versus > or equal to 34 week to 36 completed weeks GA) to ensure the intervention groups are balanced with respect to GA. Intervention allocation concealment will be achieved by using randomly permuted blocks of two, four, and six [56] to minimize risk of allocation bias.

### Concealment mechanism {16b}

Allocation will be made available only at the time of randomization when the research personnel access the online portal. Intervention allocation concealment will be achieved by using randomly permuted blocks of two, four, and six [56] to minimize risk of allocation bias, unknown to the research team.

### Implementation {16c}

Following consent and prior to the medically indicated procedure, the research nurse will randomize the infant to obtain the study intervention allocation from the online portal. Once provided the information from the site, the research nurse will inform mothers of their study arm allocation and facilitate the timing of each infants’ clinically required heel lance with the clinical team.

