### Plans to promote participant retention and complete follow-up {18b}

Follow-up is completed within minutes of finishing the procedure; therefore, it is unlikely there will be missing data due to loss to follow-up.

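### The arm is disclosed before the heel lance is timed, so the wait, exposure and losses before the lance could differ by arm; opening the allocation later avoids this cheaply

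*Protocol article*

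**What the plan says.** The order of events is set in Implementation {16c}: "Following consent and prior to the medically indicated procedure, the research nurse will randomize the infant". Once the portal has returned the arm, "the research nurse will inform mothers of their study arm allocation and facilitate the timing of each" infant's lance with the clinical team. Concealment mechanism {16b} ties disclosure to that same moment: "Allocation will be made available only at the time of randomization when the research personnel access the online portal".

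Other sections bear on what can happen between that moment and the lance:

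- Intervention description {11a} needs the mother holding the infant for at least 15 min beforehand in the SSC arm. The section on comparators {6b} has a research nurse give the sucrose and sets no condition on the mother.
- Eligibility criteria {10} applies the seven-day limit to the approach for inclusion, not to the lance.
- Criteria for discontinuing {11b} lets parents withdraw at any time, so also after they learn the arm.
- Demographic and background clinical data lists postnatal age at participation and the number of previous painful procedures. No cut-off is given for the latter count.
- Under Statistical methods {20a}, the brain-activity analysis names prior pain exposure as a potential confounder, to be adjusted for by ANCOVA if the groups differ.

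On the session itself, Outcomes {12} says: "For all infants, regardless of randomization, data collection will begin with a continuous recording of a one-minute baseline" (BL1) in the incubator or cot, followed by a first sham stimulus (NN1). Then: "The infant will then be placed in their assigned intervention group and will be re-exposed to the non-noxious control stimulus", with the lance last.

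**The concern.** Randomisation protects what is fixed before the arm is known. Here the arm is known to the nurse and the mother before the lance is timed, and one arm has a practical constraint that the other lacks. An SSC session has to fit the mother's presence. A sucrose session, as written, does not.

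Three things could then depend on the arm: how long the infant waits, how old and how pain-exposed the infant is when the event-related potential (ERP) is recorded, and whether the pair reaches a study lance at all. The protocol itself regards prior pain exposure as able to confound the primary outcome. If that exposure is counted up to the lance, part of it accrues after randomisation. The adjustment would then be triggered by a difference that allocation may have produced, and it would condition on something downstream of allocation. Blinded reading of the EEG cannot repair differences in timing or losses that arose before recording.

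**Working it through.** **1. The sequence.** Read together, the sections give: consent; randomisation and disclosure to nurse and mother; coordination of lance timing; BL1; NN1; allocated intervention; second sham; lance. The placing of disclosure before timing comes directly from Implementation {16c}. The placing of disclosure before BL1 and NN1 is an inference from the phrasing in Outcomes {12}; no section states it, and the timeline figure is not available.

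**2. The plan's own figure.** Sample size {14} gives 63 per group. With its PIPP-R inputs (difference 1, SD 2, 5% taken as two-sided, 80% power):

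n = 2 × (1.960 + 0.842)² × (2/1)² = 62.8, so 63 per group, with power 80.1%.

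The figure is reproduced. For the ERP no mean or SD is given, so the 30% basis cannot be checked. At two-sided 5% and 80% power, 63 per group detects 0.499 SD, which implies a coefficient of variation of 0.30/0.499 = 0.60. Either way the design effect is about 0.5 SD. The section states no allowance for losses.

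**3. Losses before the lance (assumed rates; the article gives none).** With loss *l* equal in both arms, power on the PIPP-R inputs is Φ(1/(2√(2/m)) − 1.96), where m = 63(1 − *l*). The number to randomise to keep 63 is 63/(1 − *l*), rounded up.

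| Loss | Power | Randomise per group |
|---|---|---|
| 0% | 80.1% | 63 |
| 5% | 78.1% | 67 |
| 10% | 75.9% | 70 |
| 20% | 70.9% | 79 |
| 30% | 65.1% | 90 |

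This shows lost power only. Losses that differ by arm would add selection, which these figures do not measure.

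**4. Arm-dependent timing (assumed sizes).** Suppose timing shifts a prognostic factor, such as postnatal age or prior pain, by *s* SD between arms, and the factor correlates *r* with the outcome. The bias is *s* × *r* SD. With the standard error √(2/63) = 0.178, let k = *s r*/0.178. The chance of a false two-sided 5% finding is Φ(−1.96 + k) + Φ(−1.96 − k).

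| *s* | *r* | Bias (SD) | False-positive risk |
|---|---|---|---|
| 0.10 | 0.1 | 0.010 | 5.0% |
| 0.25 | 0.3 | 0.075 | 7.05% |
| 0.25 | 0.5 | 0.125 | 10.8% |
| 0.50 | 0.3 | 0.150 | 13.4% |
| 0.50 | 0.5 | 0.250 | 28.9% |

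The worst case shown is half the design effect (0.25 against 0.5 SD); the mildest is negligible. Nothing in the article says where in this range the trial lies.

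**The case against.** The strongest reply is that the lance is clinically required and, according to Plans for assessment {18a}, regularly scheduled, while {11d} says no other care changes. Facilitating its timing may mean no more than fitting the EEG set-up around an existing order, perhaps within the hour. That stands as a bound on the delay, and it is why no size can be claimed. It does not remove the point: the stated order still puts knowledge of the arm ahead of the coordination, and the mother's availability is a stated need in one arm only.

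Several stronger readings are tempting, and the article does not support them:

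- A reader might infer that the baseline itself is compromised, since "research nurses and assistants completing data collection will not be blinded". Disclosure before BL1 and NN1 is only implied. Both recordings are made untreated and in the same setting in both arms, and "EEG data analysts will have no prior knowledge of study groups and assignment". This risk is weak.
- A reader might infer that age in general could drift apart. Gestational age at birth is the stratification factor and cannot change after randomisation; only postnatal age can.
- A reader might take section {18b} as a claim that no data will be missing. It says: "Follow-up is completed within minutes of finishing the procedure; therefore, it is unlikely there will be missing data due to loss to follow-up". That covers loss to follow-up only. Data management {19} separately accepts loss from equipment failure and artefact. What remains true is that {18b} does not look at the interval before the procedure.
- A reader might multiply a delay by the 12 painful procedures a day cited in the Background. That is an average over preterm infants, and the same section reports the highest exposure in the youngest and sickest. It fits stable infants of 32 to 36 weeks poorly and is not used here.
- A reader might conclude that the arms will lose infants unequally. The article shows only that they could.

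**Conclusion.** The point holds as a weakness in the stated enrolment sequence, not as a numerical error or a contradiction. The arm is known before lance timing is coordinated, no limit on the interval is stated, and the need for the mother's presence is stated for SSC alone. The interval, postnatal age and prior pain at the lance, and losses before it, are therefore open to influence by arm. The concern about the ANCOVA is conditional: it applies only if prior pain is counted past randomisation, which the article leaves open.

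The size is unknown. The range of 5.0% to 28.9% for a false finding rests wholly on assumed shifts of 0.1 to 0.5 SD and correlations of 0.1 to 0.5, and the power figures rest on assumed losses. A scheduled, clinically required lance makes long delays less likely. The change is worth making because it costs little and removes most of this route to bias, not because bias has been shown.

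**What to change.** Amend Implementation {16c} so that the REDCap allocation is opened only when a clinically required lance is already scheduled and the mother is available for that session whichever arm is drawn. Ideally, open it at the bedside after BL1 and NN1. Outcomes {12} already records both untreated in every infant, and {18a} already places the 15 min of SSC stabilisation inside the session, so the later opening fits the existing order. Concealment mechanism {16b} needs no change, since it links disclosure to randomisation and the two move together.

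State that prior painful procedures and postnatal age used as covariates are counted up to randomisation.

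For infants already randomised, report by arm the interval from randomisation to lance and the number lost before the lance, with reasons.

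The cost is a wording change and a later click by the same nurse in the same portal. The downside is real but small: some pairs will not be randomised on a given day because the mother is not available, which matters somewhat at an expected four enrolments a month. Infants whose parents change their minds before the portal is opened would simply not be randomised. Withdrawal after it remains possible, but over a much shorter interval.
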